## Abstract

**Background:**

Stroke is a leading cause of disability among adults worldwide. Evidence suggests that increased duration of exercise therapy following stroke has a positive impact on functional outcome following stroke. The main objective of this randomised controlled trial is to evaluate the impact of additional family assisted exercise therapy in people with acute stroke.

**Methods/Design:**

A prospective multi-centre single blind randomised controlled trial will be conducted. Forty patients with acute stroke will be randomised into either an experimental or control group. The experimental group will receive routine therapy and additional lower limb exercise therapy in the form of family assisted exercises. The control group will receive routine therapy with no additional formal input from their family members. Participants will be assessed at baseline, post intervention and followed up at three months using a series of standardised outcome measures. A secondary aim of the project is to evaluate the impact of the family mediated exercise programme on the person with stroke and the individual(s) assisting in the delivery of exercises using a qualitative methodology. The study has gained ethical approval from the Research Ethics Committees of each of the clinical sites involved in the study.

**Discussion:**

This study will evaluate a structured programme of exercises that can be delivered to people with stroke by their 'family members/friends'. Given that the progressive increase in the population of older people is likely to lead to an increased prevalence of stroke in the future, it is important to reduce the burden of this illness on the individual, the family and society. Family mediated exercises can maximise the carry over outside formal physiotherapy sessions, giving patients the opportunity for informal practice.

**Trial Registration:**

The protocol for this study is registered with the US NIH Clinical trials registry (NCT00666744)

## Background

Stroke is a leading cause of disability among adults in developed countries [1]. The progressive increase in the population of older people is likely to lead to an increased prevalence of stroke in the future [2]. In contrast to coronary heart disease and cancer, the burden of stroke lies with long-term disability as opposed to death. Any rehabilitation intervention that can speed recovery and reduce long-term disability would have a major impact on both the individual and the social burden of this illness. One major component of rehabilitation after a stroke is exercise therapy which serves to minimise the effects of the brain cell damage and optimise re-learning [3-5]. In this manuscript, we describe a novel protocol to increase exercise therapy time following stroke by involving the family members in the delivery of additional exercises to people with stroke.

Physiotherapists have traditionally been the mediators of exercise therapy post-stroke. Over the years different physiotherapy approaches have been advocated to promote motor recovery, including the methods of Bobath, Brunnstrom, Rood and the Proprioceptive Neuromuscular Facilitation (PNF) technique [6,7]. All of these therapy approaches are exercise based and there is evidence that physiotherapy and occupational therapy, using a mix of components from these different approaches, is significantly more effective than no treatment or placebo control in the recovery of functional independence following stroke [6]. Nonetheless, it has been suggested that the duration of exercise therapy that is delivered post stroke is, at best, 'homeopathic' [8].

Evidence from two systematic reviews [9,10] has suggested that a more intensive exercise therapy input is associated with enhanced improvement of the performance of functional activities after stroke, although the exact dose of practice required for significant functional improvements to take place is lacking. A later meta-analysis [11] also demonstrated that additional exercise therapy has a positive outcome on gait speed and activities of daily living. However this meta-analysis included studies where no formal exercise therapy was documented in the 'control' group [12-15]. The authors completed a systematic review and meta-analysis [17] that examined the effects of additional exercise therapy time by comparing randomised controlled trials that provided 'routine' therapy to the control group versus studies that provided 'routine' therapy together with 'additional' exercise therapy to the intervention group. The findings demonstrated that increased duration of exercise therapy time had a small but positive effect on activities of daily living as measured by the Barthel Index. Although the meta-analysis of the lower extremity outcome measures lacked significant findings, very few studies were included in the analysis and the results were supportive of the hypothesis that more exercise therapy improved gait speed and lower limb impairment in people with stroke. The review also highlighted the need for further randomised controlled trials with large sample sizes to evaluate the effectiveness of increased duration of exercise therapy on lower extremity outcome [17].

While the available evidence suggests that more physiotherapy is better, additional therapy is expensive and not routinely funded routinely by the National Health Service in the UK or by health insurance companies [18]. Therefore, research is now focusing on novel ways of increasing the duration of exercise therapy that occurs following stroke with minimal use of resources [8]. One suggestion has been that 'physiotherapists need to develop strategies whereby patients and caregivers take full responsibility for the bulk of therapy – for instance, training of balance, strength and endurance, repetition of simple tasks, group therapy, fitness-related training and family involvement' [19]. To date no randomised controlled trial (RCT) has evaluated the delivery of exercise by people who are not health care workers, although in a RCT by Lincoln, Parry and Vass [20], both qualified physiotherapists and physiotherapy assistants delivered two different forms of additional exercise therapy and no differences were noted between the groups. The following paper reports on the design of an evidence-based, user informed and centred RCT to evaluate the impact of increased duration of family mediated exercise (FAME) therapy in people with stroke.

### Background Work

A full systematic review and meta-analysis of previous work in this area was completed and has been accepted for publication [17]. The meta-analysis supported the theory that additional exercise therapy has a positive impact on outcome following stroke. However, the systematic review highlighted issues with patient compliance, particular patient subgroups, type of therapy, number of additional minutes of exercise therapy delivered to patients and long terms benefits of additional exercise therapy. These issues were considered in the development of the FAME RCT.

In addition, three user surveys were conducted to explore the views of potential participants in the FAME programme i.e. the individual with stroke, 'family members/friends' of people with stroke and the physiotherapists. A self-report questionnaire was administered to 100 'family members/friends' and 75 people with stroke. Two focus groups were conducted with ten expert physiotherapists working in the area of stroke rehabilitation. The results of the three user surveys supported and informed the development of the FAME trial. Family members of people with stroke indicated that they were willing to participate in the delivery of unsupervised exercises in the hospital and the home setting (n = 91). Furthermore, this method was also acceptable to people with stroke (n = 65) as an adjunct to routine physiotherapy. Physiotherapists highlighted a number of factors that influenced participation in physical therapy such level of interest and motivation of the family (n = 5), availability (n = 3) and importance of education (n = 2). 'Family members/friends' also identified reasons that would also limit participation such as work commitments (n = 24), lack of confidence (n = 20) and unsuitable treatment times (n = 13). The results of these user surveys are described elsewhere [21-24].

### Aims and Objectives of the Study

The aim of the study is to evaluate the functional recovery in two groups of primary stroke patients presenting with moderate/severe disability over a six month period through the implementation of a randomised controlled trial. The first group or the experimental group will receive routine therapy and additional lower limb exercise therapy in the form of family assisted exercises. The second group or the control group will receive routine therapy with no additional formal input from their family members. A secondary aim of the project is to evaluate the impact of the FAME programme on the person with stroke and the individual(s) assisting in the delivery of exercises.

### Ethical Considerations

The study has obtained ethical approval from four clinical sites: Saint Vincent's University Hospital Ethics and Medical Research Committee (Ref 9/5/07), Saint Colmcilles Hospital (Ref 9/5/07), the Mater Misercordiae University Hospital Research Ethics Committee (Ref 1/378/1138) and Beaumont Hospital Ethics (Medical Research) Committee (Ref 08/19).

## Methods

### Study Design

A prospective single-blind randomised controlled trial will be conducted. Forty subjects will be randomised into either an experimental group or a control group using sealed, computer generated random numbers. The progression from screening and enrollment to randomisation is illustrated in Figure legend 1.

**Figure 1 F1:**
[figure not shown]
Outline of FAME study design.

### Intervention

Members of the control group and the experimental group will receive 'routine' physiotherapy for the duration of the trial, which will be delivered by the physiotherapy staff in the hospital. In addition, participants in the experimental group will be given individualised FAME programmes to be conducted at the bedside with his/her nominated 'family member/friend'. Each programme will consist of training the 'family member/friend' with the skills necessary to carry out the exercise-training programme with the person with stroke on a weekly basis. This specialised intervention will be designed and delivered by the research physiotherapist (RG). Exercises will be designed appropriate to the participants' ability. The emphasis of the lower limb exercise intervention will be on achieving stability and improving gait velocity and lower limb strength, based on patterns derived from findings reported in a systematic review of 151 intervention studies on stroke rehabilitation [25].

Based on the output from the systematic reviews and meta-analyses [11,17], it was determined that the trial would continue for eight weeks with an expectation that at least 1200 additional minutes of family mediated exercise therapy will be delivered over this time period. Each FAME session is expected to last 35 minutes and will be conducted on a daily basis. The nominated 'family member/friend' will be requested to fill out a daily exercise diary following completion of the prescribed exercises to document compliance.

### Blinding

An independent physiotherapist blinded to group allocation will assess all participants using the battery of outcome assessments on entry to the study, on completion of the eight-week trial and finally at the three month follow-up stage.

### Outcome

The primary outcome measure used in this trial will be the lower extremity section of Fugl Meyer (FM) Assessment [26]. The FM is considered by many in the area of stroke rehabilitation to be one of the most inclusive quantitative measures of sensorimotor impairment following stroke and its use has gained international acceptance as a feasible and appropriate clinical and research tool for evaluating changes in motor impairment following stroke [27]. Excellent intra-rater and inter-rater reliability and construct validity have been demonstrated [28,29].

A series of secondary outcome measures will also be used to evaluate participants' recovery including the Motor Assessment Scale [30], the Berg Balance Scale [31], the Six Minute Walk Test [32] the Barthel Index [33], the Reintegration to Normal Living Index [34] and the Nottingham Extended Activities of Daily Living Index [35].

The Caregiver Strain Index [36], a 13-item self-report measure designed to measure strain relating to care provision, will be administered to the nominated 'family member/friend' of the person with stroke. In addition, a semi-structured interview will take place with each participant and their nominated 'family member/friend' individually, in relation to their experience of the exercise therapy programme. A physiotherapist unknown to the participant will conduct interviews. All interviews will be audio recorded.

### Participant Selection

Potential participants will be recruited from four acute hospitals. A register of all stroke patients admitted to these hospitals will be sent to the research physiotherapist on a weekly basis. Those patients who are survivors at two weeks following the onset of stroke will be assessed using the Orpington Prognostic Scale. The Orpington Prognostic Scale was developed by Kalra and Crome [37] in order to stratify stroke patients according to severity of stroke. The Orpington Prognostic Score (OPS) is a clinically derived score that incorporates measures of cognitive impairment, motor deficit, balance and proprioception. The score ranges from 1.6 (best prognosis/lowest level of disability) to 6.8 (worst prognosis/highest level of disability). It has its highest predictive power of levels of dependence when assessed at two weeks following the onset of stroke [37-39]. Only patients who achieve a score from 3.2 – 5.2 on the OPS at two weeks post stroke will be recruited to this study. This cohort of patients has been described as the *'middle group' *of stroke patients and consists of people presenting with a moderate/severe deficit following stroke [38]. It has been suggested that outcome in this band of patients depends on extrinsic factors such as the intensity and quality of rehabilitation, family support, the personality and motivation of the patient and the availability of statutory and voluntary support systems in the community [38]. The scale has been validated for both an elderly and an Irish stroke population [37,40]. The test-retest and inter-rater reliability of the OPS has also been established [40].

### Inclusion/Exclusion Criteria

Patients will be admitted to the study if they present with a formal diagnosis of first unilateral stroke, are over 18 years, are willing to give informed consent and have 'family members/friends' willing to participate in their assigned physiotherapy intervention programme. Patients will be excluded if they present with hemiplegia of a non-vascular origin, are discharged from hospital at baseline less than two weeks following stroke, have an OPS score of less than 3.2 or greater than 5.2 at two weeks following stroke onset, have a pre-existing neurological disorder resulting in a motor deficit in addition to that resulting from the stroke, present with any lower extremity orthopaedic condition such as recent fractured femur or amputation or have receptive/expressive dysphasia.

'Family members/friends' will be included if they have been nominated by the person with stroke to assist him/her in the performance of their prescribed exercises and are medically stable and physically able to assist in the delivery of exercises to the person with stroke. Suitability will be determined in liaison with the physiotherapist in charge on the patients' routine care. Family members/friends' will also be required to give informed written consent agreeing to help their 'family member/friend' with stroke in the performance of his/her prescribed exercises.

### Recruitment

The research physiotherapist (RG) will be responsible for assessing eligibility for inclusion into the study and also for obtaining informed consent from the patient and his/her 'family member/friend'. Following identification of suitable participants i.e. people with stroke and their nominated family member/friend, the aims of the project, including the role of the participant and his/her "family member/friend" in the FAME programme, will be outlined and any questions answered by RG. The person with the stroke and his/her 'family member/friend' will each receive a separate information brochure in advance of being asked to give written informed consent agreeing to participate. Participants will have seven days between receipt of the information brochure and being requested to give written permission. Following the 7-day interval, RG will answer or clarify any further questions that arise and both the person with stroke and his/her 'family member/friend' will be requested to sign a consent form in the presence of each other. If either the patient or his/her 'family member/friend' are unwilling to give written consent, they will be excluded from the study. If they decide to partake in the study, participants will be advised that they can withdraw from the study at any time and that the study will not interfere with their routine rehabilitation programme. Participants will be allocated a reference code. Names and other details that may identify the participants will be removed.

### Randomisation

To minimise the possibility of recruitment bias, a person independent of the recruitment process will complete random group allocation. Computer generated random numbers will be kept in pre-sealed envelopes in a locked drawer. Allocation will be revealed after recruitment by a telephone call from RG to an independent person, who will open the next envelope in the sequence and give the randomisation information to RG. Each envelope will only be opened on enrollment of an eligible participant. After allocation has been revealed, the appropriate intervention will be organised by RG.

### Power

Sample size is based on a power analysis. A sample size calculation was performed for the primary outcome variable, which is the lower extremity section of the Fugl-Meyer (FM). For the FM lower extremity, a change of greater than five points reflects a change greater than measurement error [42]. Power calculations indicate that a total of 40 participants are needed in order to detect with 80% power a difference of 20% between the groups at a significance level of 5%. It is anticipated that it will take 18–24 months to recruit the required number of participants.

### Analysis

All data will be collected on paper and the records will be stored by registration number in a secure cabinet. Anonymised data will be transferred to a computer database and secured using a password. An independent researcher will cross check all entries. Appropriate statistical tests will be carried out on the data using MINITAB Release 13.1.

The statistical analyses will be performed according to the 'intention to treat' principle and participants will be analysed in the group to which they were randomly assigned. Participants who withdraw from the experimental group but allow further data collection will have data collected. A 'last measurement carried forward' method is used to predict outcome in dropouts [43].

The purpose of the statistical analysis is to test the hypothesis that there will be a clinically significant difference in functional recovery between participants in the control group and the experimental group from baseline to post-intervention assessment. Firstly, the baseline scores of the participants' demographic, primary and secondary outcomes will be compared in the two groups. If necessary, adjustments for baseline variables will be made using analysis of covariance. Analyses will be carried out to examine the difference between the groups with respect to the change in the lower extremity FM test score from baseline to post-intervention assessment. Secondary outcomes will be compared between the two groups using Student's t-test or the Wilcoxon rank sum test for ordinal data. Descriptive statistics will also be used to represent demographic data.

All interviews will be tape recorded, transcribed and examined in terms of themes according to the method devised by Miles and Hubberman [44]. The responses from all participants to each question will be transferred to Microsoft Excel for examination. Following an examination of the responses to each question, a coding system will be developed in order to facilitate the identification of recurrent responses. Three researchers will be provided with the responses to all of the questions in an unencoded format; thereafter they will independently code the responses sequentially using the predefined codes. All coding disagreements will be resolved through discussion.

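### Carrying the last measurement forward sets the primary change score to zero for anyone without a week-eight Fugl-Meyer assessment, because baseline is the only earlier value

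*Protocol article*

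**What the plan says.** All places are in the protocol article.

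- **Outcome:** "The primary outcome measure used in this trial will be the lower extremity section of Fugl Meyer (FM) Assessment".
- **Analysis:** the groups are compared on "the change in the lower extremity FM test score from baseline to post-intervention assessment".
- **Blinding:** the blinded physiotherapist assesses participants "on entry to the study, on completion of the eight-week trial and finally at the three month follow-up stage". No visit lies between entry and week eight.
- **Analysis, on withdrawal:** after committing to intention to treat, the section says "Participants who withdraw from the experimental group but allow further data collection will have data collected". The next sentence is "A 'last measurement carried forward' method is used to predict outcome in dropouts". No other method for missing scores is named.
- **Power:** "a total of 40 participants are needed in order to detect with 80% power a difference of 20% between the groups". Study Design gives the same 40 as the number to be randomised, and no allowance for loss is stated.

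**The concern.** Carrying a value forward is meant to use a participant's most recent result. With this visit schedule, the most recent result before week eight is the entry score, so the rule amounts to assuming no recovery at all on the primary endpoint.

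That assumption sits badly with the trial's own premise. Eligibility is scored two weeks after stroke (Participant Selection), and consent follows a seven-day interval (Recruitment), so participants enter at about three weeks. Both arms then receive routine physiotherapy (Intervention), and the Background describes physiotherapy and occupational therapy as effective for functional recovery.

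Unequal loss is plausible. Only the experimental arm carries daily family-assisted sessions of 35 minutes, and the user surveys under Background Work list work commitments, lack of confidence and unsuitable times as limits on family participation. On the other side, the article mentions collecting data after withdrawal for the experimental group only. In arms of about 20, 20% loss is four participants, enough to move the result.

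**Working it through.** **1. The imputed value.** For a participant with no week-eight FM, the carried-forward score is the baseline score. Imputed change = baseline − baseline = 0.

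**2. Expected estimate.** Let dE and dC be the shares without a week-eight FM and μE and μC the true mean changes, with loss at random:

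expected estimate = (1 − dE)·μE − (1 − dC)·μC.

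- Equal loss d: (1 − d)(μE − μC). For a true 5 points this is 0.9 × 5 = 4.5 at 10% and 0.8 × 5 = 4.0 at 20%.
- 20% loss in the control arm only: 5 + 0.2·μC, that is 5.6, 6.0 or 6.6 for control recovery of 3, 5 or 8 points.
- 20% loss in the experimental arm only: 0.8(μC + 5) − μC = 4 − 0.2·μC, that is 3.4, 3.0 or 2.4.
- No true effect, 20% control-only loss: 0.2·μC, that is 0.6, 1.0 or 1.6 points in favour of the intervention.

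**3. Inputs for power.** The plan's N of 40 cannot be reproduced directly, because no SD is given and it is not said what the 20% is a percentage of. Solving backwards for 20 per arm, 80% power and two-sided 5%, the standardised difference is 0.886 (normal approximation) or 0.909 (t-test). For a 20% difference this means an SD of 20/0.886 = 22.6% or 20/0.909 = 22.0%. So 40 can be reached, but the SD is inferred.

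To work in FM points I take a true difference of 5, borrowed from the Power section's remark that "a change of greater than five points reflects a change greater than measurement error". The SD that gives 80% power by t-test is then 5/0.909 = 5.5. Equal allocation, control recovery of 3 to 8 points and drop-out of 10–20% are also assumptions.

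**4. Results.** Simulation of 40,000 trials per scenario, t-test on change, missing changes set to 0. Triplets are for control recovery of 3 / 5 / 8 points.

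| Loss, experimental / control | Estimate (true 5) | Power, carry-forward | Power, observed data |
|---|---|---|---|
| 0 / 0 | 5.0 | 80% | 80% |
| 10% / 10% | 4.5 | 71 / 68 / 61% | about 75% |
| 20% / 20% | 4.0 | 61 / 56 / 47% | about 70% |
| 20% / 0 | 3.4 / 3.0 / 2.4 | 45 / 33 / 21% | about 75% |
| 0 / 20% | 5.6 / 6.0 / 6.6 | 90 / 92 / 94% | about 75% |

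With no true effect, the two-sided rejection rate under carry-forward is:

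- equal 10% loss: 5.1 / 4.8 / 5.0%;
- 20% control-only loss: 6.6 / 9.3 / 14.8%.

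**5. Hand check of the lowest equal-loss figure** (20% each, control recovery 8, experimental 13). Mixing in zeros gives variance (1 − d)·SD² + d(1 − d)·μ²:

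- control: 0.8 × 30.25 + 0.16 × 64 = 34.4;
- experimental: 0.8 × 30.25 + 0.16 × 169 = 51.2.

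Standard error = √((34.4 + 51.2)/20) = 2.07, and 4.0/2.07 = 1.93. Against a critical t of about 2.02 (38 degrees of freedom), this is power of about 46%, in line with the simulated 47%. The zeros both shrink the difference and widen the spread.

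**The case against.** **Scope.** A reader might infer that every drop-out is given zero recovery. The article does not support that. Experimental-arm withdrawals who allow further data collection keep an observed week-eight score, and so do people lost only after week eight. The zero applies only to those with no week-eight FM. At the three-month visit the rule holds the first kind of loss at baseline and the second at week eight, but the stated hypothesis concerns baseline to post-intervention.

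**Direction.** A reader might also infer that the rule always hides an effect, or always inflates the error rate. Neither follows. With equal loss and no true effect, the type I error stays near 5%. Inflation in favour of the intervention needs excess control-arm loss. The experimental-only retrieval wording makes that possible, but silence about controls is not a statement that they will not be followed.

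**Size.** Drop-out, SD and recovery are all assumed, and 5 points is the article's measurement-error threshold rather than its design difference. The lowest power figures need 8 points of control recovery, which nothing in the article anchors. Part of the power loss would occur under any method: at equal loss, carry-forward itself costs about 4 to 14 percentage points at 10% (75 against 71–61) and 9 to 23 at 20% (70 against 61–47).

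**Comparator.** Loss at random makes the observed-data analysis unbiased by construction. If those lost are deteriorating or recovering poorly, zero may be nearer the truth and the observed-data analysis would itself be biased.

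All of this limits scope and size. It does not remove the mechanism, which follows from the visit schedule and the stated rule alone. Nor is this detail left to an analysis plan: the article names the method.

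**Conclusion.** The point holds for participants without a week-eight FM assessment. For them the stated rule fixes the primary change at exactly 0 in a population expected to recover. Equal loss shrinks the estimate to (1 − d) times the truth and costs power beyond what the missing data cost anyway. Unequal loss biases the estimate in a direction set by which arm loses more.

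The shrinkage formula assumes only that loss is unrelated to outcome. The power and rejection figures also depend on the assumed 5-point difference, SD of 5.5, 20 per arm and control recovery of 3 to 8 points. They show what could happen, not what the article predicts. The calculation does not show that 40 is the wrong sample size.

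**What to change.** - **Primary method.** Replace carry-forward with a baseline-adjusted analysis of all observed FM scores by randomised group. This can be ANCOVA on week-eight FM, a method the Analysis section already allows for, or a likelihood-based repeated-measures model using both post-baseline visits.
- **Carry-forward.** Keep it as a sensitivity analysis only.
- **Data after withdrawal.** State that outcome data are collected after withdrawal in both arms where participants allow it.

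The cost is a change of wording and slightly more analysis work, with no extra participants or scheduled visits. The new primary analysis relies on a missing-at-random assumption, which should be stated.

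### The hypothesis is worded as clinically significant functional recovery, but the primary and only powered analysis is change in an impairment score, with no clinically important difference defined

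*Protocol article*

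**What the plan says.** Four sections of the protocol article bear on this point.

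- **Aims and Objectives of the Study.** The aim is to "evaluate the functional recovery in two groups of primary stroke patients presenting with moderate/severe disability over a six month period".
- **Analysis, hypothesis.** The purpose is to "test the hypothesis that there will be a clinically significant difference in functional recovery". The same sentence limits the window of this contrast to the time between entry and the end of the programme.
- **Outcome.** "The primary outcome measure used in this trial will be the lower extremity section of Fugl Meyer (FM) Assessment". The section describes that instrument as "one of the most inclusive quantitative measures of sensorimotor impairment following stroke". The Barthel Index, the Nottingham Extended Activities of Daily Living Index and four other scales are secondary.
- **Analysis, primary comparison.** The groups are compared on "the change in the lower extremity FM test score from baseline to post-intervention assessment". Baseline scores are compared first, and covariance adjustment is made only if that is judged necessary. Secondary outcomes are compared by t-test or Wilcoxon rank sum test, with no visit named.

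The Power section gives two figures for FM. A change above five points exceeds measurement error, and 40 participants give 80% power for a 20% difference at the 5% level. Neither figure is described as clinically important. The Intervention and Blinding sections place the post-intervention assessment at the end of eight weeks and add a last assessment at a three-month follow-up.

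**The concern.** The hypothesis makes two claims that the primary analysis does not address directly: that the difference is one of function, and that it is clinically significant. The article's own description puts the primary outcome in a different domain, impairment. Its Background section also treats the two domains separately. It reports a small positive effect of extra exercise time on the Barthel Index, while the pooled lower-extremity results, from few studies, did not reach significance. A result on one is therefore not automatically a result on the other.

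What is at stake is how a positive trial may be read. If the FM comparison is significant, the wording of the hypothesis invites the reader to take it as proof of clinically significant functional recovery. The plan has not said which scale carries the functional claim, or what size of difference between groups would count as clinically significant. With seven clinical scales and two post-baseline visits in 40 patients, leaving this open also leaves room to choose after the data are seen.

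The timing wording adds to the uncertainty. The aim speaks of six months, the primary comparison ends at eight weeks, and the three-month follow-up has no stated origin.

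**Working it through.** **1. Construct.** The aim and the hypothesis both say functional recovery. The primary outcome is the lower-extremity FM, described in the Outcome section as an impairment measure. The Discussion gives the aim a third way, in terms of motor recovery. The FM endpoint fits the Discussion wording but not the wording of the aim or the hypothesis.

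**2. Clinical significance: the plan's own figure.** The inputs are total N = 40, power 80% and alpha 5% (Power section). Assumed: 1:1 allocation, so 20 per arm, and a two-sided test. No SD is given and the 20% has no base, so N = 40 cannot be reproduced. It can only be inverted to the standardised difference it implies:

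- Normal approximation: d = (1.960 + 0.842) × √(2/20) = 0.89 SD.
- By the t distribution with 38 degrees of freedom: d = 0.91 SD.

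**3. The smallest observed difference that is significant.**

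- t(0.975, 38) × √(2/20) = 2.024 × 0.316 = 0.64 SD.
- As a share of the detectable difference: 0.64 / 0.91 = 0.70.

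Conversion to FM points needs an SD, which the article does not give. For an assumed SD of 4 points the boundary is 0.64 × 4 = 2.6 points; for an assumed SD of 8 it is 0.64 × 8 = 5.1 points. The boundary may thus lie below or just above five points. Five points is in any case a measurement-error limit for a change score, not a threshold for a difference between group means. Whatever the SD, p < 0.05 shows a difference from zero, and nothing in the article says what larger difference would be clinically significant.

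**4. Timing.** The inputs are the Orpington assessment at two weeks after stroke (Participant Selection), a seven-day consent interval (Recruitment), an eight-week programme (Intervention) and a three-month follow-up (Blinding). One month is taken as 4.345 weeks.

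- Follow-up counted from the end of the programme: 8/4.345 + 3 = 4.84 months from baseline. Adding 3/4.345 = 0.69 for entry at three weeks gives 5.5 months from stroke.
- Follow-up counted from baseline: 3 × 4.345 = 13.0 weeks, which is 13.0 − 8 = 5.0 weeks after the programme ends.

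Neither reading gives six months from baseline. The first comes near six months only if the clock starts at the stroke.

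**5. Baseline adjustment.** Whether the primary contrast is adjusted is to be decided after looking at the baseline comparison. The primary estimate is therefore not fixed in advance, although baseline FM is collected on everyone. Analysis of covariance on baseline FM fixes it. Apart from the one degree of freedom it uses, it is generally no less precise than an unadjusted comparison of change scores.

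**The case against.** The strongest reply is that this is a matter of wording and that the analysis itself is sound. Much of that stands.

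- **The window.** A reader might infer that the hypothesis concerns six months and is tested at eight weeks. It does not: the hypothesis ends at the post-intervention assessment, as the FM analysis does. Six months appears only in the aim, and about 5.5 months from stroke could be a rounded description of it.
- **The conclusion.** A reader might infer that the trial is bound to report a conclusion its data cannot support. The article states no conclusion in advance, and nothing in it commits the authors to presenting FM as function.
- **Function is measured.** The functional scales are collected and compared between groups as secondary outcomes. A lower-limb motor endpoint also suits an intervention aimed at stability, gait velocity and leg strength.
- **Testing against zero is ordinary practice.** The 70% ratio is typical of designs with 80% power at two-sided 5% and is no defect of this trial.
- **Follow-up.** The absence of a named comparison at the last visit may be detail left to a fuller document, as may the naming of a key secondary outcome. Neither is counted here.

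What the reply does not remove is that the sentence defining the purpose of the analysis names a construct the primary outcome does not measure, by the article's own description, and a standard that the article never defines.

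**Conclusion.** The concern holds as a mismatch between hypothesis and endpoint. The stated hypothesis is clinically significant functional recovery, while the primary and only powered analysis is change in a lower-limb impairment score, and no between-group clinically important difference is defined. A significant FM result would not by itself establish the hypothesis as worded. In size, significance begins at 0.64 SD, 70% of the 0.91 SD that 40 participants can detect with 80% power, assuming 1:1 allocation and a two-sided test. No firm figure in FM points is possible without an SD.

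The timing point is separate and smaller: the six-month aim, the eight-week primary time point and the unanchored three-month follow-up need reconciling.

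The documents do not support going further. The FM comparison is not shown to be invalid or biased, and the trial is not shown to be unable to inform on function, since functional scales are compared as secondary outcomes.

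**What to change.** Restate the primary hypothesis as a between-group difference in lower-limb motor impairment (lower-extremity FM) at the end of the eight-week intervention. Analyse it by a pre-specified baseline-adjusted contrast, analysis of covariance on baseline FM, in place of adjustment that depends on the observed baseline comparison.

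Rest any claim about function on the functional scales already collected, presented as secondary evidence. Judge clinical significance from the estimate and its 95% CI, not from p < 0.05. If a between-group threshold is to be used, state it with its basis, and say what the 20% is a percentage of.

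State the starting point of the three-month follow-up and bring the six-month wording of the aim into line with it.

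The cost is a rewording of the aim, hypothesis and analysis text. It needs no new data, visits or participants. The downside is a narrower headline claim: a positive FM result would be reported as an effect on impairment, with function as supporting evidence.
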